### Blinding (masking)

Blinding will not be feasible due to the nature of the intervention; thus, neither participants nor trial personnel will be blinded in this study. However, the data analyst will be blinded to the allocation.

### Intervention

The Angolan MCH handbook is a 36-page HBR designed to keep each pregnant woman’s medical record from pregnancy through early childhood with educational information. It was developed based on the prenatal card and child health card currently being used in Angola, UNICEF educational materials, MoH documents and other materials [26]. The MCH handbook contains a log for making entries on maternal personal and health information during the course of pregnancy, delivery and postpartum; weight during and after pregnancy; infectious disease prevention and control; infant nutrition; child developmental milestones from the ages of 0–59 months; vaccination and illnesses records; and growth charts for children. The cultural appropriateness and acceptability of the handbook among pregnant women and healthcare providers have been previously assessed within a small cohort [27]. Even though the MCH handbook was generally well received among both mothers and healthcare providers, training for both groups would be required to derive the full benefits of the MCH handbook. Thus, the intervention consists of three basic components: (i) distribution of MCH handbook (the MCH handbook will be issued to pregnant women at each health facility at the HBR distribution points in the intervention arm), (ii) healthcare provider training on MCH handbook operation and (iii) community sensitisation and mobilisation among pregnant women on the use of the MCH handbook. Interventions will be delivered to pregnant women and healthcare providers in the intervention arm.

#### Pregnant women/mothers

The MCH handbook will be provided to the participant cohort during their first visit to receive MNCH services in each participating healthcare facility in the intervention arm. Explanation will be given on when and how to use the MCH handbook and on data recording. Participants will also receive health education based on the contents of the MCH handbook. Pregnant women and mothers in the study cohort attending healthcare facilities in control municipalities will continue to benefit from the traditional use of two stand-alone HBRs—the prenatal card and child health card. Pregnant women and mothers in both intervention and control municipalities will be asked to bring their MCH handbook or prenatal card and child health card to every occasion of MNCH service consultation. If a participant in either arm forgot to bring her handbook/card during a consultation, the attending healthcare provider will make a copy of the relevant recording page which will be used for keeping the record of the consultation and given to the participant.

#### Healthcare providers

Healthcare provider training on MCH handbook operation will be provided prior to distribution of the MCH handbook to pregnant women/mothers. They will be trained on skills needed for data recording into the MCH handbook, how to explain the use of the MCH handbook to pregnant women/mothers, make entries into the MCH handbook during regular consultations with pregnant women/mothers and on how to interpret data entries from the MCH handbook. Healthcare providers in the control arm will be trained on interviewing techniques for determining the date of LMP and on methods for calculating PDD only (Table 2). Healthcare providers in both intervention arms will be re-trained periodically over the intervention period.

**Table 2 Tab2:** Description of interventions

Description	Intervention arm	Control arm
Distribution of MCH handbook	x	
ToT on MCH handbook operation	x	
OJT on MCH handbook operation	x	
Assessment of LMP	x	x
Determining PDD	x	x
Community sensitisation and mobilisation on the use of the MCH handbook	x	

*ToT* training of trainers (trainers included representatives from each healthcare facility in the intervention arm), *OJT* on-the-job training for other healthcare providers, *LMP* last menstrual period, *PDD* probable delivery date

### Data collection

Study data collectors will collect data regarding MNCH services participants received. All data will be collected using a structured questionnaire by interviewer-facilitated tablet-based face-to-face interviews or abstracted from HBRs (MCH handbook in intervention arm or prenatal card and child health card in the control arm). However, where there is no record of MNCH services received in HBRs, mother’s report of service utilisation will be used in place of the missing information as previously reported by Croft et al. [28]. Data collection will be conducted at participants’ home or at a location of her choice at two time points—at baseline and at 3 months postpartum. Table 3 shows the data collection timeline for each outcome measure.

**Table 3 Tab3:** Data collection timeline for each outcome measure

Time point	Item	Data source		Location
		Survey form	HBR	
Baseline	Participant identification	x		Healthcare facility
	Socio-demographic information	x		Participants home
	Pregnancy history	x	x	
	Household characteristics	x		
	Health behaviour	x		
	ANC utilisation	x	x	
	HBR ownership and utilisation	x	x	
Follow-up (3 months postpartum)	Participant identification	x		Participants home
	HBR ownership and utilisation	x	x	
	Health behaviour	x		
	ANC attendance and maternal health	x	x	
	Infant health and feeding practices	x		
	HBR transcripts		x	

*HBR* home-based record, *ANC* antenatal care

The baseline survey will comprise eight sections designed to elicit responses on socio-demographic factors, household characteristics, pregnancy history, maternal health behaviour and HBR ownership and utilisation. Data regarding ANC attendance, maternal health behaviour, pregnancy outcomes, infant feeding practices and infant and maternal health will also be collected from women retrospectively during the follow-up survey at 3 months postpartum. Verbal responses obtained from mothers will be double-checked against record entries made in the HBRs. In cases where discrepancies occur between the mother’s report and HBR records, the latter will be prioritised. Additionally, we will verify the quality of HBR records by referring to the facility logbook data collected from a randomly selected sub-sample of women.

Interviews and data abstraction will be carried out by data collectors. Data collectors were selected from among persons with medical training or experience working with patients and were trained in tablet-based questionnaire administration and data collection processes. Training of the data collectors consisted of an overview of the study objectives, detailed description of baseline and follow-up questionnaire items and interviewing techniques, and field practice. The baseline and follow-up questionnaires were pre-tested before the start of the study. A summary of data collection timeline and questionnaire items is shown in Table 3. Interview responses and data abstracted by each data collector will be uploaded to a secure database and stored in dedicated computers on an on-going basis. Verification checks will be done on uploaded records, and attempts will be made to ensure the completeness and accuracy of collected data.

### Outcome measures

The primary outcome for this study is a measure MNCH service utilisation assessed via the proportion of women who achieved time-dependent maternal behaviour-based CoC completion as at 3 months postpartum. MNCH service utilisation and CoC completion among women in low- and middle-income countries have been found to be associated with many factors such traditional and familial beliefs, distance to healthcare facility [29, 30], health care cost [29–31], maternal education [30], perceived quality of care [29, 31] and service availability [32]. Therefore, factors influencing CoC completion may depend either on maternal behaviour and characteristics (demand-side factors) or service availability (supply-side factors). In this study, we hypothesise that distribution and utilisation of the MCH handbook will lead to maternal behaviour change leading to improved health-seeking behaviour and MCH outcomes. Consequently, the primary outcome is a time-dependent maternal behaviour-based measure of CoC completion. CoC completion will be assessed among all pregnant women who were recruited to the study during their ANC attendance. Under this measure, a time-dependent service utilisation-based CoC completion will be achieved when pregnant women receive MNCH services including a minimum number of ANC visits, facility-based delivery, postnatal care (PNC) for mother and newborn, and child vaccinations at two time points—at birth and at 2~3 months of infant age. MNCH service utilisation assessed via the proportion of women who achieve time-dependent service-based CoC completion as at 3 months postpartum will be assessed as a secondary outcome. Coverage under this measure would depend on supply-side factors, such as service availability. Thus, CoC completion will be achieved only when pregnant women/mothers have received all the required MNCH services as shown in Table 4. Details of other secondary outcomes to be assessed are presented in Table 4.

**Table 4 Tab4:** List of outcomes and definition of outcome indicators

Outcome	Definition	Type	Indicators	Details
**Primary outcome**				
Complete CoC (maternal behaviour-based)	Time-dependent composite outcome. Complete CoC is the minimum number of ANC visits + facility-based delivery + PNC for mother and newborn + child vaccinations at two time points—at birth and at 2~3 months. Includes women who attended ANC and other MCNH services only. Complete CoC = 1 when all indicators = 1	Binary	First ANC timing	Timeline divided into ≤ 20, 21~30, 31~37 and 38 weeks~ ga
			No. of ANC services	< 4 = 0, ≥ 4 = 1 (≤ 20 weeks); < 3 = 0, ≥ 3 = 1 (21–30 weeks); < 2 = 0, ≥ 2 = 1 (31~37 weeks); < 1 = 0, ≥ 1 = 1 (38 weeks)
			Facility delivery	No = 0; yes = 1
			PNC_mother	No HBR record = 0; HBR record = 1
			PNC_child	No HBR record = 0; HBR record = 1
			Vaccinations at birth and at 2 months infant age	< 2 vacc clinic visits = 0; 2 vacc visits = 1
**Secondary outcomes**				
Rate of MNCH service utilisation	Total no. of actual MCH service used per person per arm compared with an expected minimum number of service utilisation. Estimate means for each arm	Continuous	No. of ANC services	No. of women with a minimum number of ANC in each arm
			Facility delivery	No of women with facility delivery in each arm
			PNC_mother	No. of women with mother PNC record in each arm
			PNC_child	No. of women with child PNC record in each arm
			Vaccination	No. of women with child vacc record in each arm
Complete CoC (service-based)	Time-dependent composite outcome. Composite outcome including ≥ 4 ANC visits + facility-based delivery + PNC of mother and newborn + complete child immunisation up to 2~3 months. Complete CoC = 1 when all indicators = 1	Binary	First ANC timing	Timeline divided into ≤ 20, 21~30, 31~37 and 38 weeks~ ga
			No. of ANC services	< 4 = 0, ≥ 4 = 1 (≤ 20 weeks); < 3 = 0, ≥ 3 = 1 (21–30 weeks); < 2 = 0, ≥ 2 = 1 (31~37 weeks); < 1 = 0, ≥ 1 = 1 (38 weeks)
			Facility delivery	No = 0; yes = 1
			PNC_mother	No HBR record = 0; HBR record = 1
			PNC_child	No HBR record = 0; HBR record = 1
			Vaccination	< 7 records = 0; 7 records = 1
Neonatal mortality	No. of deaths within the first 28 days of life compared to the total number of deliveries in each study arm. NM = 1 when all indicators = 1	Binary	Live birth	No = 0; yes = 1
			Infant death	No = 0; yes = 1
			Date of death	Death within 28 days of birth = 1
ANC service utilisation	No. of women who receive ≥ 4 ANC visits in each arm regardless of the timing of first ANC. Adequate ANC = 1 if no. of ANC services = 1	Binary	First ANC timing	1st trimester, 2nd trimester, 3rd trimester
			Received ANC	No = 0; yes = 1
			No. of ANC services	< 4 = 0; ≥ 4 = 1
	No. of women who receive ≥ 8 ANC visits in each arm regardless of the timing of first ANC. Adequate ANC = 1 if no. of ANC services = 1	Binary	First ANC timing	1st trimester, 2nd trimester, 3rd trimester
			Received ANC	No = 0; yes = 1
			No. of ANC services	< 8 = 0; ≥ 8 = 1
Facility-based delivery	No. of facility-based deliveries in each arm.	Binary	Facility delivery	No = 0; yes = 1
Infant health check-up	Presence of at least one HBR entry from baby-well clinic attendance.	Binary	Record entry for any of current wgt, polio1, pentavalent, pneumo1 or rota1	No HBR record = 0; HBR record (for any of current wgt, polio1, pentavalent, pneumo1 or rota1) = 1
Maternal morbidity and pregnancy complication detection rate	No. of cases of specified disease conditions and pregnancy complications diagnosed by an HCP in each arm. Maternal morbidity = 1 if any indicator = 1	Binary	High blood pressure	No HBR record = 0; HBR record = 1
			Preeclampsia	No HBR record = 0; HBR record = 1
			Miscarriage	No HBR record = 0; HBR record = 1
			Stillbirth	No HBR record = 0; HBR record = 1
			Vaginal bleeding	No HBR record = 0; HBR record = 1
			Anaemia	No HBR record = 0; HBR record = 1
			Malaria	No HBR record = 0; HBR record = 1
			TB	No HBR record = 0; HBR record = 1
			HIV	No HBR record = 0; HBR record = 1
			Diabetes	No HBR record = 0; HBR record = 1
Infant morbidity rate	Total no. of disease cases attended by an HCP. Infant morbidity = 1 if all indicators = 1	Binary	Past month sickness	No = 0; yes = 1
			Sought treatment	No = 0; yes = 1
			Treatment from HP	No = 0; yes = 1
Infant mortality	No of deaths of infants < 1 year old compared to the total number of deliveries in each study arm. IM = 1 when if both indicators = 1	Binary	Livebirth	No = 0; yes = 1
			Infant death	No = 0; yes = 1
Maternal health behaviour	Prevalence of maternal health behaviour between arms with regard to tobacco use, alcohol use, PMTCT, malaria prevention, use of ITNs and family planning. Prevalence of each indicator will be compared between the intervention and control arms.	Binary	Current alcohol use	No = 0; yes = 1
			Current tobacco use	No = 0; yes = 1
			PMTCT	No = 0; yes = 1
			Family planning use	No = 0; yes = 1
			Knowledge change tobacco use	No = 0; yes = 1
			Knowledge change alcohol use	No = 0; yes = 1
Malaria prevention		Binary	ITN possession	No = 0; yes = 1
			ITN use	No = 0; yes = 1
			Malaria prophylaxis use	No = 0; yes = 1
Maternal depression	No. of cases of maternal postnatal depressive symptoms in each arm.	Binary	EPDS	< 10 = 0; ≥ 10 = 1
Infant feeding practices	Appropriate infant feeding practices including EIBF, EBF and absence of pre-lacteal feeding. Adequate if all indicators = 1	Binary	EIBF	After 1 h = 0; within 1 h = 1
			Pre-lacteal feeding	Yes = 0; no = 1
			Current BF	No = 0; yes = 1
Child vaccination	Composite outcome for the no. of complete fully vaccinated children at 3 months in each study arm. Vaccination = 1 if all indicators = 1	Binary	Polio0	No HBR record = 0; HBR record = 1
			BCG	No HBR record = 0; HBR record = 1
			Hepatitis B	N HBR record = 0; HBR record = 1
			Polio1	No HBR record = 0; HBR record = 1
			Pentavalent	No HBR record = 0; HBR record = 1
			Pneumo1	No HBR record = 0; HBR record = 1
			Rotavirus1	No HBR record = 0; HBR record = 1

*CoC* continuum of care, *ANC* antenatal care, *PNC* postnatal care, *HBR* home-based record, *MNCH* maternal, newborn and child health, *NM* neonatal mortality, *IM* infant mortality, *PMTCT* prevention of mother-to-child transmission, *ITN* insecticide-treated net, *EIBF* early initiation of breastfeeding, *EBF* exclusive breastfeeding

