### Participant cohort

The intervention will be administered to pregnant women through frontline providers of MNCH services in public healthcare facilities in Benguela. The impact of the intervention will be estimated by collecting data about maternal and newborn participants who seek care from participating facilities. All women pregnant at the beginning of the trial period and attending a public healthcare facility for MNCH services will be eligible for inclusion in the study. In order to ensure similar baseline characteristics among participant cohort across all municipalities, the study cohort will include all women confirmed to have become pregnant at the start of the trial implementation period. The participant cohort will be recruited at their first visit for any MNCH service consultation over the course of the study **(**Fig. 1). Based on the findings from a previous study [20], most pregnant women are expected to make their first visit to the healthcare facilities during the second trimester of pregnancy.

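### Table 4 scores two secondary outcomes (service-based continuum of care, infant feeding) by rules that contradict their definitions, and defines infant mortality beyond the 3-month follow-up

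*Protocol article*

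**What the plan says.** All three items are secondary outcomes in Table 4 (Methods, Outcome measures) of the protocol article.

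- **Service-based CoC.** The definition cell reads "Composite outcome including ≥ 4 ANC visits + facility-based delivery + PNC of mother and newborn", followed by complete immunisation up to 2–3 months. The ANC indicator in the same row reads "< 4 = 0, ≥ 4 = 1 (≤ 20 weeks); < 3 = 0, ≥ 3 = 1 (21–30 weeks" and continues down to "< 1 = 0, ≥ 1 = 1 (38 weeks". This is the scale used for the primary, maternal behaviour-based CoC. The definition cell and the Outcome measures text both also call the service-based outcome time-dependent.
- **Infant feeding.** The definition is "Appropriate infant feeding practices including EIBF, EBF and absence of pre-lacteal feeding", adequate only if every indicator is 1. The Table 4 footnote expands EBF as "exclusive breastfeeding". The indicators are early initiation, pre-lacteal feeding (reverse scored) and current breastfeeding yes/no.
- **Infant mortality.** The definition is "No of deaths of infants < 1 year old compared to the total number of deliveries in each study arm". The Data collection section sets two data collections, baseline and 3 months postpartum, and the section Other secondary outcomes places all outcomes at follow-up unless stated otherwise.

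**The concern.** The article itself fixes both a definition and a code for each outcome, so this is not detail that can be left to an analysis plan. Where the two differ, the outcome that is named is not the outcome that is computed.

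For service-based CoC, an analyst following the definition and one following the indicator row would classify some of the same women differently. Coded by the row, the outcome also loses any difference from the primary on ANC, although the Outcome measures text presents the two as distinct constructs, one reflecting maternal behaviour and the other service availability.

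For infant feeding, the reported proportion would be read as including exclusive breastfeeding when nothing in the row measures it. For infant mortality, a figure covering about three months would carry the name of a one-year rate. Readers could then set it against the infant mortality rate in the article's Background (54 per 1000 live births).

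**Working it through.** The point depends on no sample size, power or alpha, so there is no stated figure to reproduce. The check applies each scoring rule to the possible cases.

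**1. Service-based CoC, ANC component.** Inputs: definition cell (pass if visits ≥ 4) and indicator row (pass if visits ≥ 4, 3, 2 or 1 for first ANC at ≤ 20, 21–30, 31–37 or ≥ 38 weeks).

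| First ANC (weeks) | Row threshold | Definition threshold | Visits where they disagree | Definition / row |
|---|---|---|---|---|
| ≤ 20 | 4 | 4 | none | – |
| 21–30 | 3 | 4 | 3 | 0 / 1 |
| 31–37 | 2 | 4 | 2, 3 | 0 / 1 |
| ≥ 38 | 1 | 4 | 1, 2, 3 | 0 / 1 |

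Of the 4 × 4 = 16 combinations of timing stratum and 1 to 4 visits, 0 + 1 + 2 + 3 = 6 disagree. All six go the same way, so the row can only raise completion relative to the definition.

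Next, compare the indicators of the two composites in Table 4:

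- First ANC timing, number of ANC services, facility delivery, PNC for mother and PNC for child: identical.
- Vaccination: two clinic visits for the primary, seven records for the service-based outcome. Seven matches the seven items in the Child vaccination row.

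As coded, vaccination is the only indicator that separates them.

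The share of women affected cannot be computed. The Participant cohort section says that "most pregnant women are expected to make their first visit to the healthcare facilities during the second trimester of pregnancy". The second trimester straddles the 20-week cut, and both rules require four visits up to week 20, so that sentence does not show that most women are affected.

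**2. Infant feeding.** Take an infant breastfed within one hour, given no pre-lacteal feed, and now receiving breast milk plus other food.

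- Indicators: early initiation = 1, no pre-lacteal feed = 1, current breastfeeding = 1, so the row scores adequate.
- Definition: not exclusively breastfed, so not adequate.

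Every exclusively breastfed infant is also currently breastfed, so the row can only raise the proportion. The article gives no breastfeeding prevalence, so the amount is unknown.

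**3. Infant mortality.** The definition covers 12 months and observation ends at about 3 months: 3/12 = 25% of the window. The indicators (live birth, infant death) carry no time limit, so the conflict lies between the definition and the data collection schedule, not between the definition and its indicators.

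**4. Infant morbidity, checked for the same fault.** The definition counts illness seen by a healthcare provider. The row scores 1 if the infant was sick, treatment was sought and a provider gave it ("Infant morbidity = 1 if all indicators = 1").

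| Sick, sought, provider | Row | Definition |
|---|---|---|
| 1, 1, 1 | 1 | 1 |
| 1, 1, 0 | 0 | 0 |
| 1, 0, 0 | 0 | 0 |
| 0, 0, 0 | 0 | 0 |

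Row and definition agree in all four cases.

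**The case against.** The strongest objection concerns service-based CoC. Its definition cell opens by calling the outcome time-dependent, the Outcome measures text does the same, and the row lists timing of first ANC as an indicator. Sliding thresholds fit all three, so the four-visit phrase may be the slip. This stands to the extent that the article does not show which rule was meant. It does not remove the contradiction, because the four-visit requirement is written without qualification and Table 5 ties the sliding minimum to the primary outcome alone.

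A fixed ANC requirement also exists elsewhere. Table 4 lists separate outcomes for at least 4 and at least 8 ANC visits, whatever the timing of the first. The trial is therefore not without a fixed ANC measure; it lacks one only inside a composite. The article also says the data analyst is blinded to allocation, which limits the scope for choosing a rule to favour an arm, but does not say which rule applies.

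A reader might infer three stronger points that the documents do not support:

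- **That infant morbidity contradicts its definition.** It does not, as the four-case check shows. It will rise with care-seeking, which the trial hopes to improve, so a higher value cannot be read as more illness. That is a matter of label.
- **That requiring a live birth conflicts with a denominator of deliveries.** The indicators define the numerator event, and an infant death presupposes a live birth. Neonatal mortality is built the same way. A live-birth denominator would be a preference, not a correction.
- **That the intervention raises its own threshold by bringing women in earlier.** This is an argument about the primary outcome's design, not about a contradiction in this row. It is also limited, because the handbook is issued at the first visit, when timing is already fixed; only community mobilisation could act sooner.

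**Conclusion.** The point holds for three secondary outcomes. Service-based CoC and infant feeding each contradict themselves within one row of Table 4, and the infant mortality definition runs past the last data collection.

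For the first two the direction is certain: the coded rule can only give a proportion equal to or higher than the definition. The number of participants reclassified, and any effect on the difference between arms, cannot be derived from the article, because it gives neither the distribution of first-visit timing and visit counts nor feeding prevalences. For mortality, about a quarter of the defined window is observed.

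The primary outcome, its model and the power calculation are unaffected. The corrections should be made because they change what three reported outcomes measure and cost little.

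**What to change.** Amend Table 4 before analysis.

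1. **Service-based CoC.** Choose one rule and make the definition, the indicator row and the Outcome measures text agree. Either score ANC as < 4 = 0 and ≥ 4 = 1 whatever the week of first ANC, which matches the stated definition, makes the ANC part distinct from the primary, and requires the time-dependent wording to be clarified. Or delete the four-visit phrase from the definition and state that the ANC part equals the primary's. In the second case, point to the stand-alone ≥ 4 and ≥ 8 ANC outcomes as the fixed-threshold measures.
2. **Infant feeding.** Replace the current-breastfeeding indicator with exclusive breastfeeding at the 3-month interview. If exclusivity is not collected, remove EBF from the definition and report the component as current breastfeeding.
3. **Infant mortality.** Restate it as infant death by the 3-month follow-up.
4. **Optional.** Relabel infant morbidity as provider-attended infant illness.

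The cost is text edits to Table 4 and matching lines in the outcome sections, plus at most one question at the 3-month interview if the form lacks an exclusivity item. Sample size, randomisation and the primary analysis do not change.

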### Eligibility criteria

Participants will be eligible to join the study if they are confirmed by a healthcare provider to have become pregnant at the beginning of the trial period, had her last menstrual period (LMP) on any date from 1 March to 30 April 2019 or probable delivery date (PDD) on any date between 1 December 2019 and 31 January 2020. Participants will be selected among pregnant women and mothers within the defined cohort on their first visit to public healthcare facilities for MNCH services. Pregnant women will be excluded if they decline to participate in the study or are planning to move out of the study area while the impact evaluation study is ongoing.

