### Trial status

This article is the first protocol version. Participant recruitment started in June 2019 and is expected to be completed in June 2020.

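### Neonatal and infant deaths are set against all deliveries, and mothers enrolled after birth are not excluded, so infants already past 28 days dilute the neonatal rate and can bias the arm comparison if late enrolment differs by arm

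*Protocol article*

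**What the plan says.** In Table 4 (Secondary outcomes), neonatal mortality is "No. of deaths within the first 28 days of life compared to the total number of deliveries in each study arm". The scoring rule is "NM = 1 when all indicators = 1", and its indicators are live birth, infant death and death within 28 days. Infant mortality has the same denominator, "No of deaths of infants < 1 year old compared to the total number of deliveries in each study arm", and its event also requires a live birth.

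On who enters and when:

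- Eligibility criteria: "Participants will be selected among pregnant women and mothers within the defined cohort on their first visit to public healthcare facilities for MNCH services". The cohort is fixed by last menstrual period or by a "probable delivery date (PDD) on any date between 1 December 2019 and 31 January 2020".
- Participant cohort: "The participant cohort will be recruited at their first visit for any MNCH service consultation over the course of the study".
- Trial status: "Participant recruitment started in June 2019 and is expected to be completed in June 2020".

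Outcome measures contains one restriction by entry point: "CoC completion will be assessed among all pregnant women who were recruited to the study during their ANC attendance". It is stated for that outcome only. Statistical analysis makes the intention-to-treat set, which takes every participant by municipality of first registration, the default unless something else is stated. Nothing else is stated for the two mortality outcomes.

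**The concern.** A mortality rate should count, in its denominator, only infants who could have been observed to die. Table 4 admits two groups who could not.

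The first is stillbirths, which are deliveries but can never meet the live-birth condition. This also puts the trial's rates on a different scale from the Background section, which quotes infant mortality per 1000 live births.

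The second is infants whose mothers are first seen after the neonatal period, for example at the two-month vaccination visit. These infants have already survived 28 days. A mother whose baby died before any contact has no vaccination visit at which to be enrolled. This is survivor selection (delayed entry). The handbook is issued at the first visit, so for these infants it also came too late to influence neonatal death.

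The arm comparison is exposed because women are recruited after allocation and community mobilisation takes place only in the intervention arm. If mobilisation brings women in earlier, the intervention arm would observe deaths that go unseen in the control arm.

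**Working it through.** The protocol states no mortality rate, sample size or power for these outcomes, so there is no figure of its own to reproduce.

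**Dates.** The last probable delivery date is 31 January 2020. Recruitment is expected to finish in June 2020, which is 122 days (1 June) to 151 days (30 June) later. For a birth on 31 January, 28 days is reached on 28 February, and the three-month follow-up falls around the end of April. Entry after the neonatal period but before follow-up is therefore possible for about two months.

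**Formula.** Let *q* be the neonatal death risk among live births, *s* the stillbirth share of deliveries, and *L* the share of an arm enrolled after birth with an infant already past 28 days. Then

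observed rate per 1000 deliveries = 1000 × (1 − L) × (1 − s) × q.

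This gives late entrants zero neonatal risk and everyone else the same *q*. The values of *q*, *s* and *L* are assumptions, since the documents give none of them.

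**Stillbirths alone (L = 0).**

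| Stillbirths per 1000 deliveries | q = 27 per 1000 | 54 per 1000 (infant rate in Background) |
|---|---|---|
| 10 | 27 × 0.99 = 26.7 | 54 × 0.99 = 53.5 |
| 20 | 27 × 0.98 = 26.5 | 54 × 0.98 = 52.9 |
| 30 | 27 × 0.97 = 26.2 | 54 × 0.97 = 52.4 |

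The fall is 1 to 3% relative. Even stillbirths of 20 v 30 per 1000 in the two arms would shift the ratio only to 0.98/0.97 = 1.01.

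**Late enrolment (q = 27 and s = 20 per 1000).**

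| L | Observed rate per 1000 |
|---|---|
| 0% | 26.5 |
| 10% | 23.8 |
| 20% | 21.2 |
| 30% | 18.5 |
| 40% | 15.9 |

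**Arm comparison with no true effect.** With equal *q* and *s*, the ratio is (1 − L_int)/(1 − L_ctl), so the assumed death rate cancels.

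- 10% v 20%: 0.90/0.80 = 1.125
- 10% v 30%: 0.90/0.70 = 1.286
- 20% v 40%: 0.80/0.60 = 1.333
- Equal shares: 1.00, though both rates are too low
- Order reversed, 20% v 10%: 0.80/0.90 = 0.89

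**Is a live-birth denominator enough?** No. At 10% v 30% with s = 20 per 1000, the ratio over live births is [0.90/(1 − 0.90 × 0.02)] / [0.70/(1 − 0.70 × 0.02)] = 0.9165/0.7099 = 1.29, essentially unchanged. Restricting to women enrolled before delivery returns *q* in each arm, and so a ratio of 1.00, provided that early and late enrolees share the same risk.

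**The case against.** The strongest reply is that the late-enrolment share may be small. Participant cohort expects most pregnant women to make their first visit in the second trimester, and the recruitment text speaks mainly of pregnant women. A reader might infer from Cluster selection (45% facility delivery, 93% of children fully immunised) that first contact after birth is common. Those figures do not show it, because a woman who delivered at home may have been enrolled in antenatal care. Nor does the June 2020 end date measure usable late enrolment, since by May most of the cohort would be past the three-month follow-up. Both points stand, and they limit the size. They do not remove the rule that admits such mothers.

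Zero risk for every late entrant is also an upper bound: a mother may enrol within the first 28 days, or after losing her infant. For infant mortality, late entrants stay at risk from enrolment onward, so the ratios above do not carry over to it.

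The smaller bias could be lost in noise. Assume 4000 followed per arm (10,000 less 20%, halved). The 1.125 scenario, leaving stillbirths aside, is then about 97 v 86 deaths (4000 × 0.0243 and 4000 × 0.0216), with a 95% interval of roughly 0.84 to 1.50 before clustering. That limits what one would conclude but does not correct the estimate.

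Deliveries can be defended as a denominator that avoids conditioning on live birth, which follows randomisation. That has some force for stillbirths but none for late enrolment.

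Finally, such detail might be left to an analysis plan. But Table 4 itself fixes the denominator, and the protocol sets an entry-point restriction for one outcome and not for these.

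**Conclusion.** The point holds as a defect in a stated definition. The stillbirth part is minor, about 1 to 3% relative under assumed stillbirth rates of 10 to 30 per 1000, and nearly equal in both arms. Late enrolment is the substantive part. It understates neonatal mortality in any arm with entrants past 28 days, and it distorts the comparison only if their share differs by arm. The spurious ratio of about 1.13 (10% v 20%) to 1.29 (10% v 30%) rests on assumed shares and on zero risk in late entrants.

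A reader might go further and infer that the trial will show a false excess of deaths in the intervention arm. The documents do not support that. They give no share enrolled after birth in either arm, and the direction depends on which arm enrols earlier. Mobilisation makes earlier entry in the intervention arm plausible, no more.

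These are secondary outcomes without a power claim, and the primary outcome is already limited to women recruited in antenatal care. The change is still worth making, because the results are meant to inform nationwide scale-up.

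**What to change.** - In Table 4, define both mortality outcomes as deaths among live births to women enrolled before delivery.
- Add a sensitivity analysis that includes mothers enrolled after birth, with delayed entry at the infant's age at enrolment. Infants entering after 28 days then contribute nothing to neonatal mortality but do contribute later infant follow-up.
- Report stillbirths separately, over all births.
- Show the numbers enrolled before and after delivery by arm.
- State as a limitation that enrolment timing is itself post-randomisation. If mobilisation changes which women enrol before delivery, the restricted arms may still differ, so the restriction removes the survivor selection without guaranteeing an unbiased comparison.

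The cost is revised wording and a restriction that uses dates of enrolment and birth; the 28-day indicator already needs the birth date. Fewer infants enter the mortality analysis, and the loss grows with the late share: none at 0%, and 30% of the arm's deliveries if 30% enrol late. The primary analysis does not change.
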